### Interim analyses {21b}

Interim analysis will take place strictly for safety and ethical purposes. As soon as 20 patients per randomized group will be reached, data will be analyzed by the independent Data Safety Monitoring Board (DSMB). The trial will be stopped if the proportion of patients with major complications (Grade ≥ III) is statistically significantly higher (*p* < 0.001, Fisher’s exact test) in the HOPE group than in the control group. No statistical adjustment will be used in the interim analysis based on the sample size.

A second interim analysis will be conducted as soon as 50 per randomized group will be reached.

Results of these security analyses will be known by the DSMB members only.

### Methods for additional analyses (e.g., subgroup analyses) {20b}

There is no plan for any additional or subgroup analysis in this study.

### Methods in analysis to handle protocol non-adherence and any statistical methods to handle missing data {20c}

No missing data will be accepted for the primary endpoint and the main analysis will be based on patients with no missing data. In the event of isolated ALT or AST missing data for the primary endpoint, these data will be replaced by imputation on a case-by-case basis and this new dataset will be analyzed as a supplementary analysis. The imputation will be performed blindly by the methodologist together with the principal investigator and will be validated by the DSMB. In the event of missing or invalid data for secondary endpoints, the principal investigator and the person in charge of data analysis will decide whether these data should be considered as missing or replaced by imputation.

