### Outcomes {12}

#### Primary endpoint

Difference between the two treatment arms in the proportion of patients with early allograft dysfunction (EAD). EAD (according to Olthoff et al. [7]) is defined by the presence of at least one of the following criteria:Bilirubin level > 10 mg/dL (i.e., 171 μmol/L) on postoperative day (POD) 7INR > 1.6 on POD 7AST or ALT level > 2000 IU/L within the first 7 PODs

Primary non-function (PNF) of the graft is the very last stage of any EAD and is defined by the presence of at least one of the following criteria:Graft loss within the first 7 PODsPatient’s death within the first 7 PODs

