#### Conduct of the study

The overall schedule and time commitment for trial participants are summarized in Table 1.

**Table 1 Tab1:** Schedule of enrolment, interventions, and assessments in the HOPExt trial

Stages	V1 screening	V2 inclusion		V3	V4	V5–V11	V12	V13–V16
Time point	At inscription for LT or at pre-LT visit	D0 At hospitalization for LT	D0 HOPE group only	D0 + 6h (+/-2h) after LT	D0 + 12h (+/-2h) after LT	Day 1 to day 7 (+/-1day)	End of hospital stay	M3; M6: M9 and M12 (+/-30 days)
Actions								
Inclusion/non-inclusion criteria	X	X						
Informed consent	X							
Medical history and patient characteristics^1^	X							
MELD score	X At inscription	X						
Randomization^2^		X						
Clinical examination^3^		X					X	X
Biological analyses^4^		X (before LT)		X	X	X	X	X
Child–Pugh score		X (before LT)						
Donor characteristics^5^		X						
HOPE perfusion parameters^6^			X					
Bacteriological and fungal analyses^7^		X	X					
Intra-operative data^8^		X						
Liver biopsy^9^		X both groups	X					
Machine perfusate sample^10^			X					
ICU and hospital stay							X	
Morbidity (Clavien–Dindo score, CCI)							X	X At M3 only
Concomitant medication		X		X	X	X	X	X
Adverse events		X		X	X	X	X	X
Abdominal contrast enhanced MRI/MRCP								X At M12 only

^1^Patient characteristics: age, gender, height, weight, BMI, blood group, cause of cirrhosis, indication for transplantation, medical history (diabetes mellitus, arterial hypertension, transjugular intrahepatic portosystemic shunt), pretransplant status of residence (home, hospital ward or intensive care unit (ICU))

^2^Randomization will be performed after the harvesting team has macroscopically assessed the graft and confirmed that the graft will be harvested. After checking the inclusion and non-inclusion criteria, an online randomization tool will be used. Randomization will be stratified by center and MELD score at the time of transplantation with a cut-off of 30

^3^Clinical examination: vital signs (temperature, blood pressure, heart rate), body weight, height, BMI

^4^Biological analyses: AST, ALT, GGT, alkaline phosphatase, bilirubin, factor V, INR, platelets, creatinine, GFR, lactates. At V2 only, a pregnancy test (beta HCG) will be done for women of childbearing age

^5^Donor characteristics**:** age, gender, height, weight, BMI, blood group, length of stay in intensive care unit, cause of death, occurrence of cardiac arrest, biological test (AST, ALT, natremia)

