#### *Inclusion visit/randomization* = *V2*

#####  D0, visit 2

Verification that the consent form was signed by the patient and the investigator.

After the allocation and acceptance of the organs, the investigator will check the eligibility criteria. If the criteria are met, the liver recipient (study participant) will be randomized. The team of local investigators will be informed accordingly in order to set up the perfusion device. If the criteria are not respected, the patient will leave the study (premature termination of participation).

*Randomization*: it is important to note that absolutely no changes will be made to the national liver allocation rules. The study does not interfere or change the process of accepting or declining a liver offered to a certain patient in any way. Once a suitable recipient for the liver is identified, the recipient will be invited to come to the relevant transplant center for the surgical procedure as per routine procedure. Randomization will be performed after the allocation of the graft or after the harvesting team has macroscopically assessed the graft and confirmed that the graft will be harvested, according to the center practice. No study-related factors will be assessed before randomization. After checking the inclusion and non-inclusion criteria, an online randomization tool will be used. Randomization will be stratified by center and MELD score at the time of transplantation with a cut-off of 30.

*Prior to transplantation*: physical examination, vital signs, laboratory values (AST, ALT, GGT, alkaline phosphatase, bilirubin, factor V, INR, platelets, creatinine, GFR, lactates), MELD score (dialysis), CHILD–PUGH score (encephalopathy, ascites, albumin, prothrombin rate), and donor characteristics will be recorded. Concomitant medications and adverse events will be assessed.

*Liver transplantation*: back-table, recipient hepatectomy, and implantation will always be done by the principal investigator and sub-investigators. During recipient hepatectomy, the liver graft will be either stored in cold storage or perfused with the HOPE machine, according to the randomization. Parameters of the HOPE perfusion will be collected. Lot numbers of perfusate (Belzer-MPS) and perfusion device disposables will be recorded in the source document and eCRF.

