## Assignment of interventions: blinding

### Who will be blinded {17a}

Owing to the nature of the surgical procedure, it is not possible to blind the surgical and the anesthesiologist team for the group allocation. Because the patient cannot impact on the study outcomes after liver transplantation, there is no need to blind the patient. HOPExt is thus an open-label trial. However, in the event of isolated ALT or AST missing data for the primary endpoint, these data will be replaced by imputation on a case-by-case basis. The imputation will be performed blindly by the methodologist together with the principal investigator and will be validated by the DSMB. See the Methods in analysis to handle protocol non-adherence and any statistical methods to handle missing data {20c}. Moreover, for the analysis of the primary endpoint and some of the secondary endpoints, the data analyst will be masked to which group received the intervention (HOPE machine). A fixed code to denote each study group assignment (e.g., Group A; Group B) will be used instead.

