## Statistical methods

### Statistical methods for primary and secondary outcomes {20a}

#### Analysis sets

##### Full analysis set (FAS)

All randomized and transplanted subjects will be considered for the FAS analysis (modified intention-to-treat analysis). This population will be used for efficacy analyses.

Patients randomized in the perfusion group (HOPE) and for whom perfusion cannot be initiated for any reason will be analyzed in the intention-to-treat analysis and considered in the group in which they were randomized. This population will be used for efficacy and feasibility analyses.

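### The complete-case rule for the primary endpoint makes no exception for death or graft loss before POD 7, and the protocol never says that these events are scored as EAD

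*Protocol article*

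**What the plan says.** - **Outcomes {12}, Primary endpoint.** EAD "is defined by the presence of at least one of the following criteria:Bilirubin level > 10 mg/dL" on POD 7, INR above 1.6 on POD 7, or AST or ALT above 2000 IU/L during the first 7 PODs.
- **Same section, next paragraph.** "Primary non-function (PNF) of the graft is the very last stage of any EAD". PNF is then defined by graft loss or "death within the first 7 PODs". No sentence says that a PNF patient is scored as having EAD.
- **Item {20c}, on missing values.** "No missing data will be accepted for the primary endpoint and the main analysis will be based on patients with no missing data". Imputation is allowed only for isolated AST or ALT values, and that dataset serves a supplementary analysis. Death and graft loss are not mentioned.
- **Analysis sets {20a}.** "All randomized and transplanted subjects will be considered for the FAS analysis", and this set is named the primary population of interest.

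**The concern.** A patient who dies on POD 3 has no POD 7 bilirubin or INR. If AST and ALT stayed below the threshold, none of the listed criteria is met and two cannot be assessed. Unless PNF counts as EAD, that patient's endpoint is missing and {20c} takes the patient out of the main analysis.

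A patient retransplanted on POD 3 and alive on POD 7 raises a different problem. Laboratory tests continue daily, so POD 7 values can exist, but they describe the second graft. A failed study graft could then be recorded as free of EAD.

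In both cases the worst outcomes are removed or misclassified because of events after randomization, events that the intervention is meant to influence. The number affected can therefore differ between arms, and the bias can run either way. The arm with more early failures would look better than it is.

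**Working it through.** **1. The plan's own figure.** Inputs from Sample size {14}: 30% versus 15%, two-sided alpha 0.05, power 0.80. With the arcsine effect size used by the R package that the protocol names:

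h = 2·asin(√0.30) − 2·asin(√0.15) = 0.3639

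n = 2·[(1.960 + 0.842)/h]² = 118.55, rounded up to 119 per group.

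With 10% dropout, 119/0.90 = 132.2, rounded up to 133. Both stated figures reproduce, so no sample-size error is claimed.

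**2. What happens to each type of patient**

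| Patient | PNF counts as EAD | Literal reading of {20c} and the three criteria |
|---|---|---|
| Dies before POD 7, AST/ALT never above 2000 | EAD | Missing, excluded |
| Retransplanted before POD 7, alive on POD 7, AST/ALT never above 2000 | EAD | Scored on the second graft's POD 7 values |
| AST or ALT above 2000, then dies before POD 7 | EAD | EAD if completeness is judged on the composite; excluded if judged on each component |

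**3. Size if early losses are excluded.** Assumptions that are not in the documents: the 30% and 15% rates already include PNF, and a fraction x of each arm is lost early and excluded. Then:

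complete-case rate = (EAD − x)/(1 − x)

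For example, with 5% lost on control and 2% on HOPE: (0.30 − 0.05)/0.95 = 26.3% and (0.15 − 0.02)/0.98 = 13.3%.

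Power below uses the pooled two-proportion normal approximation, which gives 0.795 at 119 per arm with no loss (the arcsine method gives 0.801). The first power column takes 119·(1 − x) patients per arm; the second takes a full 119 analysed per arm. Differences come from unrounded rates.

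| Excluded, control / HOPE | EAD rates | Difference (points) | Power, shrunken arms | Power, 119 analysed |
|---|---|---|---|---|
| none | 30.0% / 15.0% | 15.0 | 0.795 | 0.795 |
| 3% / 1% | 27.8% / 14.1% | 13.7 | 0.73 | 0.74 |
| 5% / 2% | 26.3% / 13.3% | 13.1 | 0.70 | 0.72 |
| 2% / 2% | 28.6% / 13.3% | 15.3 | 0.82 | 0.83 |
| 3% / 3% | 27.8% / 12.4% | 15.5 | 0.84 | 0.85 |
| 1% / 4% | 29.3% / 11.5% | 17.8 | 0.93 | 0.93 |

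**4. A case with a smaller true effect.** Suppose true EAD is 25% on control and 20% on HOPE, with early loss of 2% and 5%. Then (0.25 − 0.02)/0.98 = 23.5% and (0.20 − 0.05)/0.95 = 15.8%. The apparent benefit of HOPE grows from 5.0 to 7.7 points because HOPE had more early failures.

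**5. If some early losses are retained.** Step 3 excludes every early loss. Some would already have had AST or ALT above 2000 and, if completeness is judged on the composite, would stay in as EAD. In the two control-heavy scenarios, with 119 analysed per arm, retaining half gives power of about 0.76-0.77, and retaining 80% gives about 0.78-0.79.

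**The case against.** The strongest reply is that PNF is defined under the Primary endpoint heading as the final stage of EAD and is not a separate secondary endpoint. The definition has little purpose there unless PNF patients are EAD cases. On that reading the endpoint is known to be positive, nothing is missing, and {20c} does not apply. This is probably what was intended. It stands as a reason not to say that the plan definitely drops these patients. It does not remove the point: the scoring is not stated, and the rule that is stated has no exception.

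Detailed scoring may also sit in a full protocol or analysis plan that is not shown. That is fair, but the point does not rest on missing detail. The complete-case main analysis, the three criteria and the primary population are all fixed in this article and do not fit together once a patient dies early.

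Three stronger readings are tempting and are not supported:

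- A reader might infer that POD 7 values can never exist after early graft loss. That is true after death but not after retransplantation, where the risk is misclassification.
- A reader might infer that a patient with AST above 2000 on POD 1 and a later missing sample is certainly excluded. One criterion is enough for EAD, and the article does not say whether completeness is judged per component or on the composite.
- A reader might infer that the case-by-case AST/ALT imputation can move the main result. It feeds only a supplementary analysis and is described as blinded, so it is no part of this finding.

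Finally, recruiting 133 per group gives some protection against lost power, but none against bias from outcome-dependent exclusion.

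**Conclusion.** The point holds as an unresolved conflict in the definition and analysis of the primary endpoint. Taken literally, the complete-case rule excludes patients who die before POD 7 without an established laboratory criterion, and it leaves retransplanted patients open to scoring on the wrong graft. Neither is compatible with a primary population of all randomized and transplanted patients.

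The size cannot be fixed from the documents. Under the assumed losses, the planned 15-point difference ranges from 13.1 to 17.8 points and power from about 0.70 to 0.93, depending mainly on which arm loses more patients. A reader might take the lower power figures as the expected consequence. They are not: they assume greater loss on control and exclusion of every early loss, and equal losses raise power above the planned level. What matters is that the direction depends on post-randomization events. Confidence is medium, because the intended reading may well be that PNF counts as EAD.

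**What to change.** State the following in the primary endpoint and missing-data sections, before the arms are compared:

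1. Death, or graft loss or retransplantation, by POD 7 counts as EAD whatever laboratory values exist, and is not missing data.
2. Any met criterion settles the endpoint as EAD even if other components are missing.
3. The main analysis includes every patient in the full analysis set. The few whose status is still undetermined, including those lacking POD 7 bilirubin or INR, are handled by a pre-specified statistical imputation.
4. The complete-case analysis is kept as a sensitivity analysis.

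The cost is wording and a little programming. Deaths, retransplantations and daily laboratory values are already collected. The sample size of 119 (133 with dropout) per group is unchanged if the assumed 30% and 15% already include PNF; the sponsor should confirm that they do.

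### The complete-case rule for the main EAD analysis, read literally, drops patients already known to have EAD, and the supplementary imputation has no fixed rule and no stated masking mechanism

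*Protocol article*

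**What the plan says.** All references are to the protocol article.

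- **Main analysis, {20c}:** "No missing data will be accepted for the primary endpoint and the main analysis will be based on patients with no missing data".
- **Imputation for the primary endpoint, {20c}:** for isolated AST or ALT gaps, "these data will be replaced by imputation on a case-by-case basis and this new dataset will be analyzed as a supplementary analysis". On who does it: "The imputation will be performed blindly by the methodologist together with the principal investigator and will be validated by the DSMB". Section {17a} repeats this ("However, in the event of isolated ALT or AST missing data for the primary endpoint, these data will be replaced by imputation") and refers the reader to {20c}.
- **Secondary endpoints, {20c}:** "the principal investigator and the person in charge of data analysis will decide whether these data should be considered as missing or replaced by imputation".
- **Endpoint, {12}:** EAD is present if at least one criterion is met: bilirubin above 10 mg/dL on day 7, INR above 1.6 on day 7, or AST or ALT above 2000 IU/L within the first 7 days. Primary non-function (graft loss or death within 7 days) is described as the last stage of EAD.
- **Analysis set, {20a}:** the full analysis set is every randomized and transplanted subject and is the primary population of interest.
- **Who knows the arm:** {17a} calls the trial open-label and says the surgical and anesthesiology teams cannot be blinded. The V2 visit section says "back-table, recipient hepatectomy, and implantation will always be done by the principal investigator and sub-investigators". Under {16a} the methodologist/biostatistician draws up the randomization list, and the patient's investigator receives a confirmation email. The only masking device described is a group code for the data analyst, covering the primary and some secondary endpoints ({17a}).

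**The concern.** Two things are at stake.

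First, a complete-case rule fits badly with an endpoint that any one of several criteria can satisfy. One positive criterion settles the status whatever else is missing. Requiring every component therefore discards known events. It does so most readily where missing values go with a bad course: a patient who dies before day 7 has no day 7 bilirubin or INR. Deletion of known events lowers the EAD rate in the affected arm. If it is uneven between arms, it biases the comparison in either direction.

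Second, the remedy for missing values is discretionary. What is fixed is that someone will choose, case by case, and the principal investigator is one of those choosing. That weakens the supplementary analysis, which should reassure readers about missing data, and it weakens secondary endpoints, where even the decision whether to impute is left open.

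**Working it through.** **1. The plan's own figure.** Section {14} gives 30% v 15% EAD, two-sided alpha 0.05 and power 0.80. With the arcsine method, h = 2·asin(√0.30) − 2·asin(√0.15) = 0.3639, and n = 2·((1.960 + 0.842)/0.3639)² = 118.6, so 119 per group as stated. Allowing for 10% dropout, 119/0.90 = 132.2, so 133 as stated. The sample size is not in question. I use 119 per arm below.

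**2. What the complete-case rule does to each kind of patient.** Setting {20c} against {12}:

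- ALT above 2000 IU/L on an observed day, day 7 INR missing: EAD is certain under {12}; the patient is excluded under {20c}.
- Death or graft loss on, say, day 3: last stage of EAD under {12}; day 7 components of the transplanted graft cannot exist, so the patient is excluded under a literal {20c}.
- Day 7 bilirubin above 10 mg/dL, one daily AST missing: EAD is certain; excluded from the main analysis.
- No positive criterion, day 7 INR missing: status truly unknown; excluded, and not covered by the supplementary imputation.
- No positive criterion, one isolated AST or ALT missing: status unknown; excluded from the main analysis, imputed case by case in the supplementary one.

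Only the last two groups have unknown status. The first three are in the full analysis set of {20a} with a known outcome and are lost for no statistical gain.

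**3. How much one deletion can matter.** Pooled two-proportion test, equivalent to the uncorrected chi-squared: z = (p1 − p2)/√(p̄(1 − p̄)(1/n1 + 1/n2)). The counts are assumed for illustration.

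- Near the threshold, 33/119 v 20/119: 0.2773 v 0.1681, p̄ = 53/238 = 0.2227, SE = 0.0539, z = 2.02, p = 0.043.
- One known control case dropped, 32/118 v 20/119: 0.2712 v 0.1681, p̄ = 52/237 = 0.2194, SE = 0.0538, z = 1.92, p = 0.055.
- Design rates, 36/119 v 18/119: 0.3025 v 0.1513, p̄ = 54/238 = 0.2269, SE = 0.0543, z = 2.79, p = 0.005.
- Design rates, seven known control cases dropped and none in the HOPE arm, 29/112 v 18/119: z = 2.03, p = 0.042.
- Design rates, eight dropped, 28/111 v 18/119: z = 1.91, p = 0.056.

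So one lost case can tip a borderline result, while eight one-sided losses are needed at the design rates. The borderline start is itself test-dependent: Fisher's exact test gives p = 0.061 for 33 v 20.

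**4. Blinding of the imputation.** Section {20c} names two imputers and calls the work blind. The principal investigator belongs to the transplanting team (V2 section), which {17a} says cannot be blinded. The methodologist draws up the list ({16a}). The group code in {17a} is described for the data analyst, not for these two. No step says how arm is hidden from them. For secondary endpoints, {20c} states no masking of the decision to impute.

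**The case against.** The strongest reply is that the main test is untouched by discretion: {20c} keeps imputed values in a supplementary analysis. That stands. A reader might infer that EAD status in the main analysis is left to unblinded judgement; the text rules this out.

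Other points that stand:

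- A reader might see {17a} and {20c} as contradictory on whether imputation is primary or supplementary. Section {17a} is a summary that refers to {20c}, so they do not conflict.
- A reader might say the imputers cannot be blind. The documents do not show that. The trial has eight centers, the principal investigator need not know the arm of other centers' patients, and masked records could be used. What is missing is any account of the mechanism.
- A reader might argue that the DSMB is compromised because it holds interim results ("Results of these security analyses will be known by the DSMB members only"). The stated interim comparison concerns Grade III or higher complications, not EAD, and its validation role is a check on discretion.
- The 10% allowance in {14} is for dropouts and premature terminations. It is not a rate of missing day 7 values.
- Sampling is daily with a one-day window, so gaps may be few. Analysts may also intend to count early death and graft loss as EAD, though {20c} does not say so.

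It can also be said that imputation details belong in an analysis plan that is not shown. That does not answer the point: the protocol does not defer the matter but fixes two rules, complete-case and case-by-case. An analysis plan with a fixed algorithm would have to override them.

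**Conclusion.** The point holds in this form. The main EAD analysis, taken as written, deletes patients whose EAD is already established and so departs from the full analysis set. The supplementary remedy omits day 7 bilirubin and INR, follows no fixed rule, and is called blind without a mechanism. For secondary endpoints the decision to impute rests with the principal investigator and the analyst, with no masking of that decision stated.

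The effect on the main test comes only through deletion. Its size and direction cannot be estimated, because the documents give no rate of missing day 7 values and nothing on how it might differ by arm. The p-values above are illustrations that assume 119 per arm, an uncorrected chi-squared test and losses in the control arm only. They show that the conclusion is sensitive near the threshold and much less so at the design rates. The verdict also assumes that {20c} means complete data on every component; if the authors meant only that EAD status must be determinable, the wording should say so. This should be corrected, but it does not undermine the design.

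**What to change.** Amend {20c} and align {17a}:

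1. **Classification.** In the main analysis on the full analysis set, count EAD as present if any criterion or primary non-function is observed. Treat status as missing only when no criterion is positive and a needed component is absent.
2. **Remaining unknowns.** Step 1 alone is not enough: patients with gaps would then enter only when positive, which would push the observed rate up. Replace case-by-case imputation with a fixed algorithm, for example multiple imputation from the daily AST, ALT, bilirubin and INR series with arm, center and MELD stratum, run on arm-coded data. Report best-case and worst-case bounds as sensitivity analysis.
3. **Secondary endpoints and roles.** Set a fixed, arm-masked rule for missing secondary data. Remove the principal investigator from patient-level imputation decisions, and state how the masking is done.

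Cost: revised wording and a little more programming. The four laboratory series are already collected daily to day 7, so no new data are needed.
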